### Adverse events

The clinical management recommendations given to participating FLS clinicians, as part of the iFraP DST, are evidence-based best practice, following national guidelines and in line with normal NHS care. Therefore, adverse events in this trial are expected to be minimal. Side effects of osteoporosis medications will be captured as an outcome but not reported as Adverse Events in this trial.

All serious adverse events (SAEs) either confirmed or suspected will be communicated to Keele CTU within 24 hours. An authorised medic would then conduct a causality assessment. Suspected or confirmed SAEs are to be reviewed by the DMC and reported to the Trial Steering Committee (TSC).

### Sample size

To address the objectives of the trial, 380 participants (190 in each intervention arm) need to be recruited to detect a between group effect size of at least 0.4 in the primary outcome at 2-week follow-up, with 2-tailed 5% significance and 80% power [Amendment 09, see
Table 2 and progress of the trial]. This sample size target of 380 has been calculated based on estimations that 200 participants will complete the primary outcome at 2 weeks (100 per intervention arm). It is expected that approximately 27% of patients will not receive a medicine recommendation (hence for whom the primary outcome is not relevant), 20% loss to follow-up in the primary outcome at 2-weeks, and 10% loss to follow-up because of ‘Do Not Attends’ (DNAs).

With an estimated standard deviation of 15, this translates to minimum clinically important difference (MCID) of 6 points on the DCS (scale range 0 – 100) – a difference considered to be meaningful and one that produces an effect size in the range of meaningful effect sizes recommended by the authors of the DSC
^
26
^.

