### Analysis methods

Separate a priori analysis plans will be written to describe all pre-planned trial analysis, including clinical and cost-effectiveness of the iFraP intervention alongside the process evaluation. The analysis plans will be agreed and signed off by the TSC and DMC prior to lock down of the final dataset and will be the definitive version. Consequently, only a brief outline of the planned analysis is given here.

**
*Statistical analysis*
**

A CONSORT flow diagram will describe the flow of participants through the study and will include reasons for study withdrawal if given. Descriptive statistics will be used to describe the key baseline characteristics of participants at each stage of recruitment and follow-up, and by intervention arm, to assess if there is any evidence of selection bias and to evaluate the success of the randomisation procedure.

Analysis of covariance (ANCOVA) will be used to analyse the primary outcome (the total DCS score) at the 2-week primary endpoint, by comparing the mean outcome in each intervention arm, after adjustment for any pre-specified baseline covariates. A sensitivity analysis of the primary outcome model will be conducted to explore whether study conclusions change when outcome variation between FLS clinicians is accounted for in the model. This will be achieved by adapting the ANCOVA model into a mixed model framework and incorporating a random effect term to represent the clinician who treated the patient. The magnitude of the treatment effect from this model will then be compared to that from the primary analysis in the study. We will consider using multiple imputation to impute the patient-level missing data if the missing data rate is greater than 5% for at least one patient-level outcome or predictor of interest. If multiple imputation is used, this will be regarded as the primary analysis over a complete-case analysis.

Treatment effects for secondary outcomes measured at a single follow-up time-point will be explored using similar methods to the primary outcome analysis, but with ANCOVA, logistic and ordinal regression used as appropriate for continuous, binary, and ordinal outcomes. For outcome measures collected at more than one time-point, linear mixed models will be used to model change in the outcome over time. Results will be presented either as mean or percentage differences/odds ratios alongside their associated 95% confidence intervals.

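### The stated 80% power at two-sided 5% is the case of no variation between clinicians; with clinicians nested in arms, both figures cannot hold once that variation is more than minimal

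*Protocol article*

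**What the plan says.** The Sample size section of the protocol article plans "to detect a between group effect size of at least 0.4 in the primary outcome at 2-week follow-up, with 2-tailed 5% significance and 80% power". The scale is fixed as follows: "With an estimated standard deviation of 15, this translates to minimum clinically important difference (MCID) of 6 points on the DCS (scale range 0 – 100". The target of 380 recruits rests on "estimations that 200 participants will complete the primary outcome at 2 weeks (100 per intervention arm". The inflation from 200 to 380 covers three losses only: patients given no medicine recommendation (27%), loss to follow-up (20%) and missed appointments (10%). Amendment 09 in Table 2 reopened the calculation and revised these loss rates and nothing else. No ICC, design effect or number of clinicians is given.

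Patients are randomised individually, but Trial design defines the arms by whether the treating clinician has taken the training course. Site eligibility and recruitment has the study team assign clinicians to an arm, and Clinical champion bars the champion from usual-care appointments. Each clinician therefore works in one arm only.

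Under Analysis methods, the primary analysis is ANCOVA of the total DCS score, adjusted for pre-specified baseline covariates, with no clinician term mentioned. A sensitivity analysis recasts it as a mixed model, "incorporating a random effect term to represent the clinician who treated the patient".

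**The concern.** The intervention is a consultation-skills package, and the outcome is how the patient found the decision that followed. Some variation between clinicians in that outcome is plausible, and the planned sensitivity analysis shows that the authors regard it as possible. Because clinicians are nested within arms, randomising patients does not cancel this variation: it adds directly to the variance of the difference between arms.

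The harm depends on the model. If clinician is in the model, the test keeps its 5% level but has less than 80% power, and a null result says less about a 6-point effect than the sample size section implies. If clinician is left out, as in the outlined primary analysis, the rejection rate stays fairly high, but the standard error is too small and the false-positive rate exceeds 5%. The second harm is the larger one under the analysis as planned.

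**Working it through.** **Inputs from the protocol article.** Difference 6 points, SD 15, two-sided 5%, 100 completers per arm, and losses of 27%, 20% and 10% (Sample size). Four sites (Progress of the trial), each with at least two clinicians (Site eligibility and recruitment), so at least four clinicians per arm.

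**Assumptions, because the documents give no figure.** Clinician ICC of 0.01, 0.02 or 0.05; k = 4, 8 or 12 clinicians per arm; equal caseloads of m = 100/k completers.

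**Step 1: reproduce the plan.** SE = 15 × √(2/100) = 2.121. Power = Φ(6/2.121 − 1.96) = Φ(0.868) = 80.7% (80.4% with the t distribution). The requirement is 99 per arm. Recruitment is 200/(0.73 × 0.80 × 0.90) = 380.5, and 380 recruits yield 199.7 completers. Everything reproduces, with almost nothing spare.

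**Step 2: how much ICC the margin absorbs.** With design effect DE = 1 + (m − 1) × ICC, power falls below 80% once the ICC exceeds about 0.0008 (k = 4) or 0.0017 (k = 8). It falls below 78% at about 0.003 or 0.006.

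**Step 3: a test that accounts for clinician.** SE becomes 2.121 × √DE, and power = Φ(6/(2.121√DE) − 1.96). A second version uses the non-central t distribution with 2k − 2 degrees of freedom. The difference detectable at 80% power is (1.96 + 0.842) × 2.121 × √DE = 5.94√DE (normal approximation).

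**Step 4: the planned ANCOVA without a clinician term.** The test uses the SE of 2.121, while the estimate really varies with 2.121√DE. Rejection rate at a true 6 points = Φ(0.868/√DE). True type I error = 2 × [1 − Φ(1.96/√DE)].

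| k per arm | ICC | DE | Power, clinician in model: normal | Same, t with 2k − 2 df | Detectable difference (points) | ANCOVA without clinician: rejection at 6 points | Same: true type I error |
|---|---|---|---|---|---|---|---|
| 4 | 0 | 1.00 | 81% | 66% | 5.9 | 81% | 5.0% |
| 4 | 0.01 | 1.24 | 72% | 57% | 6.6 | 78% | 7.8% |
| 4 | 0.02 | 1.48 | 64% | 50% | 7.2 | 76% | 10.7% |
| 4 | 0.05 | 2.20 | 48% | 36% | 8.8 | 72% | 18.6% |
| 8 | 0 | 1.00 | 81% | 75% | 5.9 | 81% | 5.0% |
| 8 | 0.01 | 1.12 | 76% | 70% | 6.3 | 80% | 6.3% |
| 8 | 0.02 | 1.23 | 72% | 66% | 6.6 | 78% | 7.7% |
| 8 | 0.05 | 1.58 | 62% | 55% | 7.5 | 76% | 11.8% |
| 12 | 0 | 1.00 | 81% | 77% | 5.9 | 81% | 5.0% |
| 12 | 0.01 | 1.07 | 78% | 74% | 6.2 | 80% | 5.9% |
| 12 | 0.02 | 1.15 | 75% | 71% | 6.4 | 79% | 6.7% |
| 12 | 0.05 | 1.37 | 68% | 64% | 6.9 | 77% | 9.4% |

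Worked row (k = 4, ICC 0.05): m = 25, DE = 1 + 24 × 0.05 = 2.20, √DE = 1.483. With clinician in the model, SE = 3.146 and power = Φ(1.907 − 1.96) = 48%. Without it, rejection = Φ(0.868/1.483) = 72% and type I error = 2 × [1 − Φ(1.321)] = 18.6%.

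**Step 5: possible offset from covariates.** With k = 4, covariates explaining 20% of the variance bring power back to 81% at ICC 0.01. At ICC 0.02, even 30% gives only 79.4% (normal approximation).

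**The case against.** Several points on the other side stand.

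Nothing is miscalculated: 99 per arm, 80% power and 380 recruits all reproduce. A reader might infer an arithmetic error, but the documents do not show one.

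A reader might take the table to mean that the primary analysis has only 36% to 78% power. That is not so. Those figures belong to a test that includes clinician, whereas the outlined primary ANCOVA would reject 72% to 80% of the time on the same grid. This does not rescue the stated design, because the rejection rate is held up by a type I error above 5%.

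The t-based column should not be read as the effect of clinician variation alone. The degrees-of-freedom penalty already lowers power to 66%, 75% and 77% at ICC 0 for 4, 8 and 12 clinicians per arm.

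A reader might also say that the protocol expects clinician variation. It does not: it plans a check in case there is some. Nor is zero ICC strictly required, since covariate adjustment could offset a small ICC. But the sample size section claims no such gain, and Table 1 has no baseline DCS to adjust for.

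Finally, the article condenses a fuller protocol and defers to a separate definitive analysis plan. That excuses missing detail. It does not qualify a power statement that the article sets out in full, or the choice of primary and sensitivity model that it outlines.

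**Conclusion.** The concern holds in this form: 80% power at two-sided 5% for a 6-point difference with 200 completers is the zero-ICC case. Once clinicians vary by more than a very small amount, both figures cannot hold together unless covariates make up the loss.

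Over the assumed grid, a test that accounts for clinician has 48% to 78% power (normal approximation), or 36% to 74% with few-cluster degrees of freedom, and a detectable difference of 6.2 to 8.8 points. The planned ANCOVA keeps 72% to 80% rejection at a true type I error of about 6% to 19%. These ranges rest on assumed ICCs, assumed numbers of clinicians and equal caseloads. Four clinicians per arm is the minimum that the site criteria imply, not an estimate, so the documents do not fix the shortfall at one number.

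This should be fixed. It is an unstated independence assumption in a trial that already plans the model needed to deal with it.

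**What to change.** Keep the recruitment target. Adding patients under the same clinicians is an inefficient remedy. With 4 per arm and ICC 0.02, 80% power (normal approximation) would need 99 × 0.98/(1 − 99 × 0.02/4) = 192.1, so 193 completers per arm or 386 in all. At ICC 0.05 no number suffices, because 99 × 0.05/4 exceeds 1.

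- In the sample size section, state the number of clinicians per arm and an assumed ICC range with its basis.
- Restate power, or the detectable difference, at 200 completers over that range. Include the ICC 0 line under the same degrees of freedom, and label 80% as the zero-ICC case.
- In the analysis section and the analysis plan, make the clinician random-effect model the primary analysis, with a small-sample degrees-of-freedom correction, and keep the ANCOVA without clinician as the sensitivity analysis. Restating power alone would leave the type I error problem in place.

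The cost is a paragraph in the sample size section and a swap of two analyses that are both already planned. No extra patients are needed. The stated power becomes less favourable and the primary confidence interval wider.

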### Analysis methods

Separate a priori analysis plans will be written to describe all pre-planned trial analysis, including clinical and cost-effectiveness of the iFraP intervention alongside the process evaluation. The analysis plans will be agreed and signed off by the TSC and DMC prior to lock down of the final dataset and will be the definitive version. Consequently, only a brief outline of the planned analysis is given here.

**
*Statistical analysis*
**

A CONSORT flow diagram will describe the flow of participants through the study and will include reasons for study withdrawal if given. Descriptive statistics will be used to describe the key baseline characteristics of participants at each stage of recruitment and follow-up, and by intervention arm, to assess if there is any evidence of selection bias and to evaluate the success of the randomisation procedure.

Analysis of covariance (ANCOVA) will be used to analyse the primary outcome (the total DCS score) at the 2-week primary endpoint, by comparing the mean outcome in each intervention arm, after adjustment for any pre-specified baseline covariates. A sensitivity analysis of the primary outcome model will be conducted to explore whether study conclusions change when outcome variation between FLS clinicians is accounted for in the model. This will be achieved by adapting the ANCOVA model into a mixed model framework and incorporating a random effect term to represent the clinician who treated the patient. The magnitude of the treatment effect from this model will then be compared to that from the primary analysis in the study. We will consider using multiple imputation to impute the patient-level missing data if the missing data rate is greater than 5% for at least one patient-level outcome or predictor of interest. If multiple imputation is used, this will be regarded as the primary analysis over a complete-case analysis.

Treatment effects for secondary outcomes measured at a single follow-up time-point will be explored using similar methods to the primary outcome analysis, but with ANCOVA, logistic and ordinal regression used as appropriate for continuous, binary, and ordinal outcomes. For outcome measures collected at more than one time-point, linear mixed models will be used to model change in the outcome over time. Results will be presented either as mean or percentage differences/odds ratios alongside their associated 95% confidence intervals.

Descriptive statistics (numbers and percentages) will be used to describe patients experience of their FLS appointment and exploratory analysis conducted to explore whether patients’ perception of their fracture risk changes following the intervention, and whether their post intervention perception of risk is more in line with their predicted fracture risk (as calculated by their Fracture Risk Assessment (FRAX®) score. In addition, we will also explore whether patients’ level of worry about falls and fractures changes following their FLS consultation and whether such changes are similar in both trial arms.

**
*Economic evaluation*
**

The economic evaluation will comprise a within-trial cost-effectiveness and value of information (VoI) analysis to determine whether the iFraP intervention is cost-effective compared with usual care. The health economic evaluation protocol will be published separately.

**
*Process evaluation*
**

A mixed methods process evaluation, in line with the MRC guidance
^
36
^, will explore perceived acceptability of iFraP amongst patients and clinicians, what components of iFraP were delivered and how (fidelity), how much of iFraP was delivered (dose), whether iFraP results in a change in outcomes (e.g. shared decision-making, medicine initiation rates) and how, context affects implementation of iFraP and outcomes. Various methods, including semi-structured interviews, CRFs, consultation recordings, and DST analytics will capture data for the process evaluation. The process evaluation protocol will be published separately.

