### Site eligibility and recruitment

To be eligible for this trial, FLSs must:

decide, recommend, and communicate osteoporosis drug recommendations to patients in a face-to-face and/or remote consultation.be situated in England, with a minimum of 2 clinicians.

The Royal Osteoporosis Society (ROS), existing clinical networks and the NIHR Clinical Research Network (CRN) will be used to identify eligible FLSs for the iFraP study. The selection of potential FLS sites will consider capturing variation in the FLS’s service provision (informed by the iFraP national survey of FLSs
^
22
^) and characteristics of the local population. Identified FLSs (face-to-face or remotely) meet with study team members who fully explain the study and describe the study requirements. Informed consent for FLSs to participate will be provided by the research lead/authorised person in each service, acting as ‘guardian’ for patients in their care, following agreement with the team clarifying willingness to undertake the iFraP intervention. FLS clinician agreement to take part in the trial will be captured as part of the written agreement completed by the research lead/authorised person in each service. FLS consent to participate in the trial is formalised through a Sponsor-site agreement. The number of FLSs approached, declining, or considered not eligible will be recorded.

The research sites receive local management approval, trial specific training and trial administrative procedures prior to the start of recruitment into the trial. FLS clinicians and other team members (e.g. FLS administrators) will also be provided with study-specific training including training on completion of study documentation, using the REDCap database, good clinical practice as applicable to research and the maintenance of the study site file and study records.

FLS clinicians are allocated by the study team to intervention arm or comparator usual FLS NHS care arm, considering seniority and years of experience, to try and achieve balance of skills and experience in both arms of the trial.

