
Participants randomised to iFraP-i will be scheduled their FLS appointment with an FLS clinician that has completed the iFraP Consultation Skills Training Course. iFraP-i is delivered in one consultation which may be conducted face-to-face or remotely by video or telephone, depending on a variety of local factors including service commissioning, staffing, and the impact of COVID-19, usually lasting approximately 30 minutes. During the appointment, the FLS clinician will use the iFraP DST and provide the patient with iFraP information resources, such as an individualised summary of the appointment (the ‘personal Bone Health Record’), printed from the iFraP DST in-person (if consulting face-to-face), or sent by post (if consulting remotely). After the consultation, the Bone Health Record will also be shared with the patient’s GP.

**
*Comparator usual FLS NHS care (iFraP-u)*
**

Participants randomised to this comparator arm will be scheduled their face-to-face or remote FLS appointment with an FLS clinician delivering usual FLS NHS care. At present, usual FLS care does not use Decision Support Tools to support patient-clinician discussion, nor do FLS clinicians have access to the iFraP Consultation Skills Training Course or information resources that would be provided as part of the iFraP intervention. FLS clinicians delivering iFraP-u will be offered the opportunity to partake in the intervention training at the end of the trial.

**
*Crossover and post-trial care*
**

Participants cannot crossover from one arm of the trial to the other. Any protocol deviations that occur during the trial will be recorded and their impact assessed for future trial conduct and the final data analysis plan.

Participants’ clinical care after the FLS appointment returns to normal FLS NHS care.

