### Progress of the trial

Recruitment commenced in May 2023. A review of recruitment and follow up rates with the DMC and TSC in July 2023 and with the TSC in October 2023 identified slower recruitment and lower follow up rates than anticipated. The TSC recommended that an additional FLS site is recruited to participate in the trial. This resulted in three key amendments to the number of sites, target sample size and recruitment duration and rate:

1. On 14th July 2023, the REC approved an amendment to include one additional FLS research site, increasing the number of participating FLS sites from three to four.2. The original protocol inflated the sample size of 200 to a target of 328 patients. This target assumed that approximately 32% of patients would not receive a medicine recommendation (hence for whom the primary outcome is not relevant) and accounted for 10% loss to follow-up at 2-weeks. When reviewing these assumptions with the DMC and TSC, approximately 27% of patients did not receive a medicine recommendation, 20% were loss to follow-up at 2-weeks and a further 10% losses were observed due to ‘Do Not Attends’ (DNAs). Therefore, to achieve 200 responses to the primary outcome at two weeks, the sample size target was inflated to 380.3. During the first 6 months of trial recruitment an average of 27 patients per month were recruited across three sites. Following an addition of an extra site, an amended total recruitment period of 11 months is required to meet the revised sample size (n=380). The monthly target for recruitment was therefore adjusted from 63 to 44.

Protocol amendments are described in detail, along with rationale for change, in
Table 2.

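### Each clinician delivers one arm only, yet the primary ANCOVA has no clinician term; if DCS scores vary between clinicians, its standard error is too small and type I error exceeds 5%

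*Protocol article*

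**What the plan says.** Patients are randomised individually, stratified by FLS (Randomisation), but the arms are defined by the clinician. Trial design separates them by whether the clinician has completed the iFraP training. Under Site eligibility and recruitment, the study team assigns each clinician to one arm. Under Interventions, "Participants randomised to iFraP-i will be scheduled their FLS appointment with an FLS clinician that has completed the iFraP Consultation Skills Training Course", and usual-care clinicians are offered the training only once the trial is over. The Clinical Champion is trained and may not deliver usual care.

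An eligible FLS must "be situated in England, with a minimum of 2 clinicians", and Progress of the trial records an amendment "increasing the number of participating FLS sites from three to four".

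Analysis methods names ANCOVA on the total DCS score, adjusted for pre-specified baseline covariates, as the primary analysis. A mixed model with a random effect for the treating clinician is a sensitivity analysis, to "explore whether study conclusions change when outcome variation between FLS clinicians is accounted for in the model". The comparison it specifies is this: "The magnitude of the treatment effect from this model will then be compared to that from the primary analysis in the study".

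Sample size plans to "detect a between group effect size of at least 0.4 in the primary outcome at 2-week follow-up", "with 2-tailed 5% significance and 80% power". It mentions no ICC and no design effect.

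**The concern.** Randomising patients does not make their outcomes independent here. Within a site, patients in the two arms see different clinicians, so a difference between clinicians in how they conduct the conversation becomes part of the difference between arms. Stratifying by or adjusting for FLS does not remove it, because the clinician difference lies within the site. An ANCOVA that treats the 200 patients as independent counts this variation as information about iFraP.

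At stake are the p-value and confidence interval for the primary outcome. The specified comparison also looks at the quantity least affected. With similar caseloads the clinician random effect hardly moves the estimate and mainly widens its standard error, so agreement in magnitude says little about whether the primary interval is valid.

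**Working it through.** **1. The plan's own figures.** Inputs from Sample size: difference 6, SD 15 (effect size 0.4), two-sided 5%, 80% power, 100 evaluable per arm, and losses of 27%, 20% and 10%.

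- n per arm = 2 × (1.960 + 0.842)² × (15/6)² = 98.1, rounded up to 99, or 198 in total (stated: 200).
- Power with 100 per arm = 80.7% (80.4% by noncentral t).
- Recruitment = 200 / (0.73 × 0.80 × 0.90) = 380.5 (stated: 380).

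The figures reproduce with a design effect of 1, that is, with no allowance for clinicians.

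**2. Number of clinicians.** Four sites with at least two clinicians each means at least one per arm per site, so at least 4 per arm. This is a floor; the actual number is not given. I use k = 4, 8 and 12 per arm.

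**3. Type I error of the primary test.** Assumptions: 100 analysed per arm, equal caseloads m = 100/k, ICC 0.01 to 0.10.

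Design effect DE = 1 + (m − 1) × ICC. The true standard error is √DE times the one ANCOVA reports. Actual two-sided type I error = 2 × [1 − Φ(1.96/√DE)].

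Example, k = 4 and ICC 0.05: m = 25, DE = 1 + 24 × 0.05 = 2.20, √DE = 1.483, 1.96/1.483 = 1.32, type I error 18.6%.

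| Clinicians per arm | ICC 0 | 0.01 | 0.02 | 0.05 | 0.10 |
|---|---|---|---|---|---|
| 4 (m = 25) | 5.0% | 7.8% | 10.7% | 18.6% | 28.8% |
| 8 (m = 12.5) | 5.0% | 6.3% | 7.7% | 11.8% | 18.1% |
| 12 (m = 8.3) | 5.0% | 5.9% | 6.7% | 9.4% | 13.7% |

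A simulation of 20,000 null trials per scenario, with four sites and site as a fixed effect, agrees. At ICC 0.01, 0.02, 0.05 and 0.10 it gave 8.0%, 10.4%, 19.8% and 30.3% for 4 per arm; 6.1%, 7.7%, 12.3% and 19.1% for 8; and 5.8%, 7.0%, 9.4% and 13.9% for 12. At ICC 0 it gave 4.9% to 5.0%. Adjusting for site does not remove the inflation.

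**4. The specified comparison.** With equal caseloads the mean over patients in an arm equals the mean of its clinicians' means. The two models then give the same unadjusted estimate whatever the ICC. Only the standard error, interval and p-value differ.

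**5. Power once clinicians are allowed for.** 200 evaluable patients, effect size 0.4, noncentrality = 0.4 / √(2 × DE/100). The small-sample column uses a noncentral t with between-clinician degrees of freedom = 2k clinicians − 4 site terms − 1 arm term, so 3 for k = 4 and 11 for k = 8.

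| Clinicians per arm | ICC | Normal approximation | Small-sample df |
|---|---|---|---|
| 4 | 0.01 | 72% | 42% |
| 4 | 0.05 | 48% | 27% |
| 8 | 0.01 | 76% | 68% |
| 8 | 0.05 | 62% | 54% |

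**The case against.** Five points can be made for the plan.

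- **The inflation is conditional.** A reader might infer that the false-positive rate is known to exceed 5%. The article does not support that: it gives no ICC, and at ICC 0 the rate is exactly 5%. A positive ICC is plausible, since the intervention trains consultation skills, clinicians are balanced on seniority and experience, and the plan itself considers variation between clinicians. It remains an assumption. This stands.
- **Four per arm is an entry criterion, not the design.** Colleagues taking part in role play together, and a Champion who mentors intervention clinicians, suggest more than one intervention clinician per site, though they do not prove it. With 8 intervention and 4 usual-care clinicians the average design effect gives 7.1%, 9.2%, 15.4% and 23.9% at ICC 0.01, 0.02, 0.05 and 0.10. This stands as a reason not to lead with the highest figures.
- **The check is not blind.** A reader might infer that the sensitivity analysis cannot reveal the problem. That goes too far: its stated aim is whether conclusions change, the mixed model yields its own interval, and unequal caseloads would move the estimate somewhat. What remains is that the one comparison specified is of magnitude, which alone is a weak check.
- **The article is an outline, and the separate analysis plan is definitive.** This excuses missing detail on covariates, degrees of freedom and ICC reporting. It does not excuse the ranking, because the article itself says which model is primary and which is sensitivity.
- **The remedy costs power.** This is true, and the cost must be stated. But the 80% is available only if clinicians do not differ; otherwise the ANCOVA hides the loss.

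**Conclusion.** The point holds in conditional form. Clinicians are nested in arm by design, and the model named as primary ignores them. For any positive clinician ICC the primary interval is too narrow and the test rejects too often. The size is a range and not a figure. It rests on 100 analysed per arm, equal caseloads, ICC 0.01 to 0.10 and an unknown number of clinicians: about 6% to 14% with 12 per arm, 6% to 18% with 8, and 8% to 29% at the floor of 4.

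Confidence is high on the direction given a positive ICC, and limited on the size. The documents do not show that the trial has only 4 clinicians per arm, that the inflation is certain, or that the planned check would necessarily miss it. Because this affects the primary inference and can be corrected before the dataset is locked, it should be changed.

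**What to change.** **Primary outcome.** Make the mixed model already described the primary analysis of the DCS: arm and FLS as fixed effects with the pre-specified covariates, clinician as a random effect, and Kenward-Roger or Satterthwaite degrees of freedom because clinicians may be few. Keep the ANCOVA without a clinician term as the sensitivity analysis. State that the standard error, confidence interval and p-value will be compared as well as the estimate. Report the clinician ICC and the number of clinicians and patients per clinician in each arm.

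**Secondary outcomes.** Use the same structure for continuous outcomes. The two degrees-of-freedom corrections belong to linear mixed models and do not carry over directly to the logistic and ordinal models. There, specify a clinician-level random effect or another clustering method suited to few clusters.

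**Power.** State that the 80% assumes no clinician clustering, and restate power for 200 evaluable patients over an assumed ICC range. At ICC 0.05 it is about 48% (4 per arm) or 62% (8 per arm) by normal approximation, and about 27% or 54% with small-sample degrees of freedom.

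**Cost.** A wording change in the protocol and the analysis plan before the dataset is locked. No new data are needed, since the planned sensitivity model already requires the identity of the treating clinician, and no extra enrolment is asked for. The price is a wider interval and an openly lower power.
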